**Figure 2 F2:**
[figure not shown]
Study design and recruitment flow.

A health economic analysis is also included with the objective of ascertaining the cost effectiveness of the intervention compared to standard care, and the potential benefit of the intervention in terms of number of life years saved. The health economic analysis is modeled on similar evaluations conducted in a cancer/medical setting [30]. The costs associated with each mode of information delivery are collected from each site by the study coordinator, including printing costs, blood collection fees, and courier fees. Surgeons’ and genetic counselors’ time (minutes) associated with discussing TFGT with each patient is recorded by each practitioner on a record sheet, which is faxed to the study coordinator after the relevant appointment. In Stage II, a retrospective health professionals’ survey will be conducted to determine health care providers’ attitudes toward and experiences of the TFGT process. The survey is targeted to breast surgeons, medical oncologists, radiation oncologists, and breast care nurses involved in the delivery of TFGT. Ethics approval has been received from the institutional review board for each site.

## Methods

### Participants

A woman is eligible to participate if she is aged less than 50 years at diagnosis of invasive breast cancer or ductal carcinoma *in situ* and has not had a mastectomy for her current cancer or radiotherapy at the time of invitation. The eligibility and exclusion criteria are presented in detail in Figure 3. The patient must have (A) either a strong family history of breast and/or ovarian cancer, specifically (i) three or more affected relatives including the patient on one side of the family or (ii) two or more affected relatives including the patient on one side of the family and a high-risk feature [31], or (B) in the absence of a relevant family history, the woman must have at least one of the following high risk features: bilateral breast cancer; and/or Ashkenazi Jewish heritage, and/or a triple negative tumor. 

**Figure 3 F3:**
[figure not shown]
Study inclusion and exclusion criteria.

### Intervention

The educational materials entitled ‘Making a decision about treatment-focused genetic testing’ were developed by the research team on the basis of the information preferences expressed by women in our qualitative interviews. The development and pilot-testing of the educational materials is reported in detail elsewhere [27]. The brief educational pamphlet contains information about: (i) what TFGT is; (ii) the purpose of TFGT; (iii) why a woman might consider having TFGT; (iv) what is involved in having TFGT; and (v) different outcomes of TFGT and their implications for the patient and her family.

Participants in the intervention group who elect to have TFGT receive an intake interview over the telephone, when their family history is collected, including cancer history and ages of diagnoses of the patient’s biological first- and second-degree relatives, approximately one week prior to their results disclosure appointment.

### Control

Participants allocated to the control group receive pre-test genetic counseling ranging from 40-60 minutes in duration, which typically covers the following topics:

(i) Explanation of hereditary breast cancer and the breast cancer ‘protection genes’ (*BRCA1*/*BRCA2*);

(ii) Discussion of patient’s risk of having a *BRCA* mutation based upon their family history or other high-risk features;

(iii) What a *BRCA1/BRCA2* mutation search involves;

(iv) Explanation of the potential advantages and disadvantages of genetic testing according to the patient’s family history and personal situation;

(v) An explanation of what type of information genetic testing may or may not provide and the implications for treatment/prevention;

(vi) Checking patient understanding of the concepts discussed;

(vii) Obtaining informed consent for genetic testing if the patient wishes to proceed.

Participants in the control group are contacted by telephone by the genetic counselor prior to their pre-test appointment for a brief intake interview equivalent to the intervention group.

### Genetic testing and disclosure of test results

Participants are offered TFGT with a turn around time of 10 working days from blood draw, free of charge, as part of the study.

All participants who elect to have TFGT receive their test results in a face-to-face appointment at a family cancer service attached to their treating hospital, regardless of their randomization. The results disclosure appointment of 20-40 minutes typically covers the following content:

(i) Disclosure and explanation of the test result;

(ii) Implications of the result for the patient’s personal risk of another primary breast cancer and risk of ovarian cancer;

(iii) Options for reduction of future risk of these cancers;

(iv) Implications of the test result for genetic relatives;

(v) Communicating test results with genetic relatives, informed consent and privacy issues;

(vi) Checking patient understanding of the concepts discussed.

### Recruitment

Recruitment commenced in July 2010 and details of the process are presented in Figure 2. The study coordinator sends the first questionnaire and a consent form to each patient who agrees to participate, either online or by post. The patient is randomized immediately after the study coordinator receives her completed questionnaire and consent form.

### Measures

#### Patient questionnaires

The four self-administered patient questionnaires are completed over a 12 month period. A summary of the measures included at each time point is provided in Figure 4. Details of the measures are provided below:

(i) *Demographic, disease- and family history-related data:* Sociodemographic data are collected including age, marital status, language spoken at home, education, employment, occupation, and parity.

(ii) *Decisional conflict scale (DCS):* This 10-item validated scale measures decisional conflict in relation to genetic testing choices, including uncertainty about alternatives, modifiable factors contributing to uncertainty, and perceptions of effectiveness of decision-making [32]. Response options are 0 = ‘yes’ 2 = ‘unsure’ and 4 = ‘no’. Scores are converted to a 0-100 scale by summing scores, dividing by 10 and then multiplying by 25, with higher scores indicating greater decisional conflict [33].

(iii) *Impact of Event Scale (IES):* The 15-item IES, which has been validated in this population [34], is being used to measure the frequency and severity of breast cancer specific worry. Response options are 0 - ‘not at all’, 1 = ‘rarely’, 3 = ‘sometimes’, and 5 = ‘often’. A total score is obtained by summing the items (range 0 to 75) with a higher score indicating more distress.

(iv) *Hospital Anxiety and Depression Scale (HADS):* The 14-item HADS is a widely used measure of emotional disturbance and has two subscales measuring anxiety and depression [35]. Each question has four possible responses. Responses are scored on a scale from 0 to 3. A total scale score is obtained by summing each item (range 0 = 42) with a higher score indicating more general distress.

(v) *Knowledge of TFGT:* Ten items were purpose designed and pilot-tested for this study to assess knowledge and understanding of TFGT. There are three response options including ‘true’, ‘false’ and ‘don’t know’. Correct responses are assigned a score of ‘1’ and incorrect or ‘don’t know’ responses are scored ‘0’. Correct answers are summed to give a score out of 10 (range: 0-10).

(vi) *Acceptability of the educational materials* (intervention group only): have The length, pace, amount of information, and balance and whether other family members used the educational materials is assessed using five structured response categories [36].

(vii) *Family involvement in decision-making about genetic testing:* Two items assess whether other family members participated in the decision-making process.

(viii) *Test-Related Distress and Positive Experiences* (women who choose testing only): This measure includes 10 items from a validated questionnaire (the Multidimensional Impact of Risk Assessment Scale) [37] assessing distress (six items) and positive experiences (four items) about genetic testing. Response options range from 0 = ‘never’ to 5 = ‘often’ with scores ranging from 0 to 30 and 0 to 20 for the distress and positive experiences scales, respectively.

(ix) *Decision Regret Scale (DRS: Genetic Testing Choice*): This five-item scale measures distress or remorse after health care decisions, and has excellent psychometric properties [38]. It has been adapted to measure decision regret in relation to women’s decision regarding genetic testing. Response options range from 1 = ‘strongly agree’ to 5 = ‘strongly disagree’. Two items are reverse scored. Scores are converted to a 0-100 scale by subtracting 1 from each item and then multiplying by 25. To obtain a final score, each item is summed and averaged with higher scores indicating more regret (0 = no regret and 100 = high regret) [39].

(x) *Decision Regret Scale (DRS: Surgical Decisions):* A second version of the DRS measures decision regret in relation to women’s decisions about bilateral mastectomy and RRSO.

(xi) *Patient preferences regarding TFGT:* Two items have been adapted from a previous study conducted by our team exploring patient preferences and perceived survival benefits among younger women with early breast cancer considering endocrine therapy [40]. The items assess: (i) the minimum perceived mutation carrier rate required to make TFGT worthwhile; and (ii) how much women would be willing to pay for such a test.

**Figure 4 F4:**
[figure not shown]
Patient measures administered during the study.

Clinical information will be gathered from participants’ medical records retrospectively including family history of breast and/or ovarian cancer; date of diagnosis; tumor size and grade; nodal and receptor status; menopausal status at diagnosis; type and date of surgery (lumpectomy, unilateral mastectomy and BM, axillary surgery, reconstruction surgery, RRSO–including intended RRSO); adjuvant treatment/s, and *BRCA* mutation status.

#### Health professionals’ questionnaire

The 17 item online retrospective survey has been developed for the current study using items adapted from a previous health service evaluation [41] and also based upon expert input from the research team. The survey will be administered once all participants have been recruited to the study. Oncology health professionals who have participated in the current trial or who were directly involved in the care of women involved in the trial, will be invited to participate via email with a secure link provided therein to the consent form and online self-report questionnaire. The survey aims to assess these health professionals’ attitudes and experiences of the TFGT trial, including their satisfaction with the trial and the TFGT process; perceived success of the trial; the amount of health professionals' time invested in providing the TFGT service; perceived barriers and enablers to delivering TFGT effectively; aspects of the TFGT process that could be improved; and suggestions for integrating TFGT into clinical practice.

### Statistical power

It is estimated that less than 10% of breast cancer patients of all ages will be eligible for the study.

A total sample size of 128 has 80% power to test the non-inferiority of the intervention on the primary outcome, the Decisional Conflict Scale (DCS). For the DCS, a non-inferiority margin will be -10 units, that is, the intervention group will be considered no worse than the standard care group if the 95% CI of the mean difference in DCS between the two groups lies wholly above -10 units. The DCS has 10 items, with the following response options: ‘Yes’, ‘Unsure’ and ‘No’ to items such as: ‘Do you know which options are available to you?’ The DCS total score ranges from 0 to 100 and thus a non-inferiority margin of -10 units on the DCS corresponds to only one of the 10 items having been endorsed as ‘No’ instead of ‘Yes’. The power calculation is based on a 5% significance level (2-sided), a true mean difference of zero units and a conservative SD of 20 units.

### Statistical analysis

An intention-to-treat analysis will be conducted on the differences in means between the intervention and standard care groups on psychological and decision-related outcomes. Linear regression shall be used for each outcome measured at 12 months, adjusting for the patient baseline scores. Further multivariate analyses will be used if preliminary analyses suggest a need to adjust for potential confounding variables (e.g. sociodemographic characteristics including age, parity, education, mutation status, and family history). In order to investigate whether, and how, patient outcomes differ between the intervention and standard care groups over time, the repeated measurements (T1, T2, T3, T4) shall be analyzed using linear mixed effects [42]. This approach will appropriately adjust for the repeated measures per person and allows for missing values. For all analyses, appropriate model checking will be conducted and where required, alternatives to linear regression will be used (e.g., logistic regression, if there is a need to dichotomise an outcome variable).

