### Design

This is a multicenter randomized controlled trial which is being conducted at nine hospital sites located in three states in Australia (New South Wales, Victoria and Queensland) in two stages. The study protocol adheres to CONSORT guidelines [29]. The study design is presented in Figure 2. In Stage I, 140 eligible patients are being randomized to receive either EM or SC. Randomization is in a 1:1 ratio and is achieved through a computerized random sequence, which is generated by an independent person. Each number in the sequence is printed and placed in an unmarked envelope such that allocation is concealed from the study coordinator until randomization occurs. It is not possible to blind participants to their allocation because they become aware of it once the genetics staff arrange patients’ genetic counseling appointments. The primary outcome measurement is level of decisional conflict regarding TFGT. The secondary behavioral and psychological outcome measures include: (i) uptake of TFGT; (ii) uptake of BM; (iii) cancer-specific distress; (iv) general anxiety and depression; (v) distress associated with decision to have genetic testing; (vi) level of decision regret regarding TFGT and surgical decisions, and (vii) family involvement in decision-making. Over the course of the study, four questionnaires will be administered: at baseline (prior to randomization); one week after receiving education about TFGT; 3 weeks after receipt of genetic testing result (or at the equivalent time point for those who do not have genetic testing or who choose not to receive their test result); and 12 months after study enrolment. 

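### The intention-to-treat comparison of means uses a 12-month regression that, without imputation, omits women with no 12-month score; the article does not say whether it or the mixed model gives the non-inferiority interval

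*Protocol article*

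**What the plan says.** The Statistical analysis section of the protocol article opens with "An intention-to-treat analysis will be conducted on the differences in means", covering the psychological and decision-related outcomes. The estimator follows at once: "Linear regression shall be used for each outcome measured at 12 months, adjusting for the patient baseline scores".

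The same section then plans a linear mixed model on T1 to T4, to see whether and how the arms differ over time. Only this second model is said to be one that "allows for missing values".

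The Statistical power section sets the decision rule: "For the DCS, a non-inferiority margin will be -10 units", judged by the 95% confidence interval of the mean DCS difference. It names neither the visit nor the model that yields that interval. On size it states "A total sample size of 128 has 80% power to test the non-inferiority of the intervention on the primary outcome", while the Design section says "In Stage I, 140 eligible patients are being randomized to receive either EM or SC".

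**The concern.** A regression of the 12-month score on arm and baseline score needs a 12-month score. Unless values are imputed, a woman who answers the first three questionnaires but not the fourth contributes nothing to it, although she was randomised and partly followed. Calling the comparison intention-to-treat suggests that all randomised women count. The article recognises that questionnaires will be missing, but attaches the remedy to the other model.

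This matters more in a non-inferiority trial because the error can favour the conclusion sought. Higher DCS scores mean more conflict. If women in the pamphlet arm with high earlier conflict return the last questionnaire less often, and the control arm does not lose its high scorers in the same way, the remaining pamphlet-arm women look better than the arm as a whole. Participants know their allocation, so response that differs by arm is plausible, though nothing in the article shows that it occurs.

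**Working it through.** **1. The plan's own figure.** Inputs from Statistical power: "The power calculation is based on a 5% significance level (2-sided"), 80% power, margin of size 10, and "a true mean difference of zero units and a conservative SD of 20 units". Normal approximation: n per arm = 2 × (1.960 + 0.842)² × 20² / 10² = 62.8, so 63 per arm or 126 in total. With the t distribution, 64 per arm gives 80.1% and 63 per arm gives 79.5%. The stated 128 is reproduced.

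**2. Room for loss.** 140 − 128 = 12 women, and 12/140 = 8.6%. No attrition rate is given, so the rates below are assumptions.

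**3. Power among completers.** Noncentral t, margin 10. The unadjusted column uses SD 20. The other two use the residual SD 20 × √(1 − r²), where r is the assumed correlation between baseline and 12-month DCS: 18.3 at r = 0.4 and 16.0 at r = 0.6.

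| Loss | Completers of 140 | Unadjusted | r = 0.4 | r = 0.6 |
|---|---|---|---|---|
| 10% | 126 | 79.5% | 85.9% | 93.6% |
| 15% | 119 | 77.2% | 83.9% | 92.2% |
| 20% | 112 | 74.6% | 81.6% | 90.6% |

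The planned regression is baseline-adjusted, so the two right-hand columns are the relevant ones, and none of their entries is below 80%. At a weaker correlation of 0.3 and 20% loss, the normal approximation gives 79.2%. Power is therefore not the main issue.

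**4. Bias among completers.** If a fraction p of one arm is missing and those women score g units above that arm's completers, the completer mean is too low by p × g.

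Simulation A assumed a true difference of 10 units against the pamphlet, SD 20, equal correlation between visits, pamphlet-arm dropout rising with the T2 score, and random dropout at the same average rate in the control arm. Estimates from the completer regression:

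| Correlation | 10% loss | 20% loss |
|---|---|---|
| 0.3 | 9.52 | 9.33 |
| 0.5 | 9.55 | 9.07 |
| 0.7 | 9.62 | 9.26 |

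The shortfall runs from 10 − 9.62 = 0.38 to 10 − 9.07 = 0.93 units, or 4% to 9% of the margin.

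Simulation B assumed pamphlet-arm dropout of 35% after a high T3 score and 5% otherwise, control dropout of 10%, and correlation 0.4 to 0.6. The completer bias was 0.56 to 0.73 units toward the pamphlet. An analysis that also used T1 to T3 was biased by less than 0.05 units.

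**5. What the largest shift would mean.** At r = 0.5 and 20% loss, the standard error is 20 × √(1 − 0.25) × √(2/56) = 3.27. The shift is 0.93 / 3.27 = 0.28 standard errors. At a true difference equal to the margin, the chance of wrongly declaring non-inferiority rises from 2.5% to about Φ(−1.96 + 0.28) = 4.6%.

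**The case against.** **The text does not say that non-inferiority rests on completers.** A reader might infer that every woman without a 12-month questionnaire is dropped and that the trial's main conclusion therefore depends on completers. The article does not support that. It writes no exclusion rule, does not rule out imputation, and does not assign the decisive interval to the 12-month regression. This objection stands and limits the point to a conditional one. The regression is still the natural reading: the decision rule is a difference in means between arms, and the analysis section takes up differences in means and names this regression next.

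**The mixed model is also a between-arm comparison.** This is true. A woman without a 12-month score is lost from one of two planned comparisons, not from both. What remains open is which one decides.

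**Missing-data rules belong in the analysis plan, and intention-to-treat often just means analysed as randomised.** Both are fair, and the lack of an imputation rule in a condensed article is not criticised here. The point concerns an estimator that the article does state, beside a better-suited one that it also states.

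**The gain depends on material not shown.** Figure 4 lists which measures are taken at which visit. The mixed model helps only if the DCS is collected after baseline and before the deciding visit. If the deciding DCS is the one taken a week after education, 12-month attrition and both simulations are beside the point. This stands as a condition on the fix.

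**The effect is small, and a large power loss is not shown.** The unadjusted column might tempt a reader to conclude that the trial is underpowered. That column ignores the planned baseline adjustment, and the article gives neither an attrition rate nor a correlation. A larger bias can be built, for example 15% missing with a 15-unit gap in one arm only (0.15 × 15 = 2.25 units), but nothing in the article supports that gap.

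**Conclusion.** The point holds in conditional form. The article pairs an intention-to-treat label with an estimator that is a completer analysis unless values are imputed. It credits only the other model with handling missing values, and leaves open which model decides non-inferiority.

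If the 12-month regression decides, dropout that depends on earlier conflict and differs by arm would bias the DCS difference toward no worse. The size is modest, about 0.4 to 0.9 units of a 10-unit margin. It rests entirely on assumed dropout patterns, an SD of 20 and assumed correlations between visits. Power below 80% is not established. The change is worth making because the error runs in the favourable direction and the better-suited model is already planned.

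**What to change.** State that the DCS non-inferiority contrast and its 95% confidence interval come from the planned mixed model, read at the named primary visit. Include all randomised women with DCS data, arm as randomised, visit as a categorical factor, the arm-by-visit interaction and baseline DCS. This applies provided the DCS is collected at one or more post-baseline visits before the primary visit. Keep the baseline-adjusted single-visit regression as a supportive analysis.

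Add one tipping-point sensitivity analysis that worsens the missing pamphlet-arm scores step by step until the interval crosses the margin, and report how large a worsening that takes.

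The cost is a few sentences in the analysis plan and a little extra analysis, with no new data or patients. The drawback is that the mixed model relies on data being missing at random. The tipping-point analysis shows how far the conclusion depends on that.

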## Discussion

This study aims to compare the impact, efficiency and safety of two different ways of offering information about TFGT to women using (a) brief educational materials or (b) standard care (pre-test genetic counseling). In June 2012, 110 participants have been recruited to the study. During the recruitment period, several issues have been encountered that warrant consideration to ensure successful integration of TFGT into standard clinical practice for women diagnosed with breast cancer in the future.

